**Figure 2 F2:**
[figure not shown]
**Appliances to be used in the study. (A)** Twin-block appliance (active MAS). **(B)** Sham MAS (non-active MAS).

#### Sham MAS design (non-active MAS)

This consists of two non-active upper and lower acrylic plates resembling the design of the active MAS, but without any component to protrude the mandible (Figure 2).

### Randomization

Participants will be randomly assigned to either a sequence starting with the Twin-block or the Sham MAS. Thereafter, participants will wear the appliances for 3 weeks separated by a 2-week washout period. Participants will not be told whether they wear the active or the non-active appliance. Each night of wear time will be recorded by parents using diaries.

Patients will be allocated to active or sham treatment using four randomized n-of-4 blocks that are balanced for treatment sequence (Sequence 1: Twin-block MAS first followed by Sham MAS; sequence 2: Sham MAS first followed by Twin-block MAS; Figure 3). Allocation will be concealed in opaque envelopes, and disclosed by a member of the research team (MF) immediately after enrolment. Participant flow is illustrated in (Figure 3).

**Figure 3 F3:**
[figure not shown]
**Participants' flow in the study**.

## Outcome measurements and stepwise procedure

### Sleep data

Home-based abbreviated polysomnography, Type III (Polese et al., 2010), will be performed using a portable monitoring unit (Embletta MRP PG-XS-ENU, Natus Neurology Incorporated, Ontario, Canada).

PSG recording channels in the Embletta unit will be comprised of one electromyographic (EMG) channel, a finger pulse oximetry, nasal airflow (using a nasal pressure catheter), nasal and mouth thermistry, thoracic and abdominal respiratory effort bands (two piezoelectric belts will be placed around the rib cage and abdomen and monitor respiratory movement), body position sensors, and a microphone attached to the nasal cannula extension. The following variables will be measured: pulse oximetry, airflow, respiratory effort, snoring sound, body position, and EMG of the masseter muscle. This equipment has previously been validated for the diagnosis and management of SDB (Dingli et al., 2003; Skomro et al., 2010; Fredheim et al., 2014; Park do et al., 2015).

The portable device is set up through the use of a separate application software, RemLogic-E version 3.4 (Embla system, Natus Europe, Planegg, Germany). Channels are configured and identified, sampling rates set, filtering options defined, recording timing (on/off times), etc. through the same software.

Home-based PSG data will be collected four times for each participant at baseline and after treatment with Twin-block or Sham MAS, with the support of a research assistant (Figure 4).

**Figure 4 F4:**
[figure not shown]
**The study design is a crossover randomized controlled trial**. Sixteen patients will be randomly assigned to two sequences; both sequences include a 3-week treatment period with active and non-active (sham) mandibular advancement splints but in a different order (Active followed by Non-active and Non-active followed by Active). Treatment periods will be separated by a 2-week washout period. Assessments will be taken at baseline (T0) and four times throughout the study. PSF, polysomnography; Ceph, Cephalograms; PSQ, Pediatric Sleep Questionnaire; BASC-2, Behavior Assessment System for Children, second edition; OSA-18, Quality of Life questionnaire; ESS, Epworth Sleepiness Scale (ESS).

The AHI will be calculated according to the American Academy of Sleep Medicine (AASM) criteria for scoring pediatric respiratory sleep studies (Berry et al., 2012). AHI is the main outcome of interest and sleep position will be considered in AHI scoring because sleep related obstructive respiratory events in children occur more commonly in the supine sleep position (El-Kersh et al., 2016).

### Snoring frequency

Snoring sounds will be assessed by analyzing audio recordings recorded using the portable PSG equipment. Snoring will be scored manually by listening to the audio recording using RemLogic-E software and the result will be reported as: total snoring time, relative snoring time, number of snoring episodes, average snoring episodes, and longest snoring episode.

The use of audio recordings is one of the recommended methods to aid visualize snoring oscillations (Berry et al., 2012). Embletta MPR microphone (an analog omnidirectional condenser microphone) attached to nasal cannula will record the snoring sounds. All signals will be fed into analog/digital (A/D) converter with a 200 Hz sampling rate (each channel has 200 points or samples per second; Shiomi et al., 2011). For optimal visualization of snoring, a high-pass filter to remove very low frequencies (20 Hz) and a low-pass filter to remove high frequencies (3 kHz) will be used, this will permit acquiring relevant information of snoring sounds (Pevernagie et al., 2010).

Subjective reports of snoring frequency will also be collected by parents using daily diaries throughout each treatment period (Figure 4).

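### The 200 Hz sampling rate stated for all signals is incompatible with the 20 Hz to 3 kHz band and the scoring by listening specified for snoring

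*Protocol article*

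**What the plan says.** Under Snoring frequency, the protocol article derives its objective snoring outcome from the microphone of the portable unit: "Snoring sounds will be assessed by analyzing audio recordings recorded using the portable PSG equipment". The method is manual: "Snoring will be scored manually by listening to the audio recording using RemLogic-E software". Five measures of snoring duration and count are to be reported.

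On digitisation it says "All signals will be fed into analog/digital (A/D) converter with a 200 Hz sampling rate", and it explains the figure: "each channel has 200 points or samples per second". For the snoring sound it then specifies "a high-pass filter to remove very low frequencies (20 Hz") and "a low-pass filter to remove high frequencies (3 kHz) will be used", so that the relevant snoring information is kept.

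Under Sleep data, the microphone is listed among the unit's recording channels, and the set-up software is described: "Channels are configured and identified, sampling rates set, filtering options defined". No separate rate for the audio channel is given anywhere. Snoring frequency is also collected by parents in daily diaries.

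**The concern.** One short section fixes a sampling rate, a frequency band and a scoring method, and the rate does not support the other two. The band reaches 3 kHz, while a channel with 200 samples per second stops at 100 Hz. A scorer listening to such a channel would not hear the sound that the band is meant to preserve.

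If the recorder were configured as written, the audio-based measures could not be produced by the stated method in any of the planned recordings (16 children × 4 nights = 64). Content lost or misplaced at conversion cannot be recovered later. This is not a detail left to a fuller document, because the article states all three elements itself.

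**Working it through.** **Inputs** (all from Snoring frequency)

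- Sampling rate fs = 200 Hz, given again as 200 samples per second in each channel. The two statements agree, and the second rules out a total shared across channels.
- High-pass cut-off 20 Hz; low-pass cut-off 3,000 Hz.
- Scoring by listening.

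**Step 1: what 200 Hz can represent.** Highest faithful frequency = fs / 2 = 200 / 2 = 100 Hz. The usable part of the planned band is therefore 20 to 100 Hz. On an octave scale this is log2(100/20) = 2.3 of log2(3000/20) = 7.2 octaves.

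**Step 2: what a 3 kHz band needs.** Minimum rate = 2 × 3,000 = 6,000 samples per second, to be exceeded in practice. Ratio to the stated rate: 6,000 / 200 = 30.

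**Step 3: can the placement of the filter rescue the text?**

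- *Digital filter, after conversion.* The cut-off must lie below fs / 2 = 100 Hz. A 3 kHz low-pass cannot be built at 200 Hz; a standard filter-design routine refuses it.
- *Analogue filter, before conversion.* It lets 100 to 3,000 Hz through. Unless a further anti-alias filter removes that content, a frequency f appears at |f − 200 × round(f/200)|. So 440 Hz appears at |440 − 400| = 40 Hz, and 1,030 Hz at |1,030 − 1,000| = 30 Hz.

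Neither placement yields the stated band.

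**Step 4: what happens to sound bursts.** Artificial noise bursts (1.5 s in every 4 s) were reduced to 200 samples per second. The anti-alias filter used was an 8th-order low-pass at 90 Hz.

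| Burst content | Amplitude kept, no anti-alias filter | Amplitude kept, with anti-alias filter |
|---|---|---|
| 30–90 Hz | 1.00 | 0.95 |
| 110–400 Hz | 1.00 | 0.05 |
| 110–2,900 Hz | 1.00 | 0.02 |

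Higher-frequency content is thus nearly removed, or it survives in amplitude at false frequencies. The timing of a burst may therefore remain visible in a trace even where its sound is lost. These are synthetic signals. They show the mechanism and do not estimate how many real snores would be missed.

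**The case against.** The strongest reply is that this is a conflict in the text and not demonstrated data loss. Sampling rates are set in the software, and scoring by listening fits a faster audio channel, with the 200 Hz sentence worded too broadly. That stands as a possibility. But the article does not say so, and the text would still need correcting.

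It is also fair that the outcome is secondary, that its five measures are durations and counts and not spectral quantities, and that the parent diary does not depend on the audio. The discussion already concedes possibly limited power for secondary outcomes. These points lower the severity. They do not reconcile the figures, and the diary does not supply the five audio measures.

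A reader might infer more than the documents support:

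- *That nothing above 100 Hz is recorded.* Without an anti-alias filter it is recorded, but at the wrong frequency. The article does not say whether the converter has such a filter.
- *That about 97% of the snoring information is lost.* The retained share of linear bandwidth is (100 − 20) / (3,000 − 20) = 2.7%, but that is not a share of snores or of snoring minutes.
- *That other noise would be indistinguishable from snoring.* This is not shown, and airflow and respiratory effort are recorded at the same time.
- *That the masseter EMG is spoiled too.* The article gives no EMG frequency band, so 200 Hz contradicts nothing it states about that channel.

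**Conclusion.** The specification is wrong as written: a rate of 200 samples per second per channel is incompatible with a 20 Hz to 3 kHz band and with scoring by listening. The gap is a factor of 30 in sampling rate (200 against more than 6,000 per second).

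The consequence is conditional. If the microphone channel really runs at 200 Hz, the five audio-based snoring measures cannot be obtained by the stated method, in up to 64 recordings, and this cannot be undone. If the channel runs faster, the error is one of reporting. In neither case does it follow that snoring cannot be measured at all, and no effect on AHI, the sample size or the parent diary has been shown. This should be corrected before recording starts, but as a problem in a secondary outcome it does not threaten the trial's main conclusion.

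**What to change.** Before the first recording, check the microphone channel in the recorder's set-up software and state its actual sampling rate in the protocol, separately from the other channels.

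- *If the 3 kHz band and scoring by listening are kept:* set that channel above 6 kHz, for example 8 kHz. Assuming the unit allows this, the cost is a configuration setting and storage. With an assumed 16-bit sample and 9-hour night, that is 8,000 × 2 bytes × 9 × 3,600 s ≈ 0.52 GB per night.
- *If the unit cannot record that fast:* set the low-pass below 100 Hz, replace listening with scoring of the low-frequency trace, and describe the outcome as a low-frequency snore signal. This costs a short text edit and a narrower claim for the five measures.

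If 200 Hz turns out to be a misstatement for the audio channel, correcting that sentence is enough.

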### Growth hormone levels

Blood samples will be taken from all participants by a certified phlebotomist in a medical laboratory (Southern Community Laboratories). Growth hormone will be indirectly assessed by determination of insulin-like growth factor-1 (IGF-1) levels (Laron, 2001).

Two samples will be collected at the end of each treatment period and collected in a non-fasting state in the morning to early afternoon.IGF-1 concentrations were assayed using a human IGF-I quantikine ELISA Kit (PDG100, R&D Systems, Minneapolis, USA). The human IGF-1 immunoassay employs the quantitative sandwich enzyme technique. Samples will be stored in a −80°C freezer until batch assayed by a technician who will be blinded to the treatment period. Disposal of medical wastes will follow the World Health Organization guidelines (WHO, 2007, 2016), and disposal with appropriate karakia (Māori prayer) will be offered to participant if needed.

### SDB and daytime sleepiness questionnaires

SDB associated symptoms will be assessed using the Pediatric Sleep Questionnaire and Sleep Related Breathing Disorder (SRBD) subscale (PSQ-SRBD; Chervin et al., 2000). This 22-question tool will be filled in by parents and includes questions about history of breathing difficulties during sleep, snoring quality and frequency, daytime signs of sleepiness, Inattention and hyperactivity, in addition to few other questions about morning headache, obesity, enuresis, and delayed growth. The optimal SRBD scale cut-off to indicate presence of SDB would be 0.33 (i.e., ≥33% of the 22 question-items answered positively; Chervin et al., 2000).

Daytime sleepiness and related behavioral disturbances will be assessed using the Epworth Sleepiness Scale (ESS; Manni et al., 1999). ESS is a self-administered questionnaire with 8 questions; it provides a measure of a person's general level of daytime sleepiness, or their average sleep propensity in daily life. It has become the standard method for making this assessment. The ESS asks people to rate, on a 4-point scale (0–3), their usual chances of dozing off or falling asleep in eight different situations or activities that most people engage in as part of their daily lives. The total ESS score is the sum of 8 item-scores and can range between 0 and 24. The higher the score, the higher the person's level of daytime sleepiness (Johns, 1991, 1993; Manni et al., 1999). To make this questionnaire suitable for children, the question about alcohol will be removed and the questionnaire will be completed by parents/caregivers. PSQ-SRBD and ESS questionnaires will be administered four times during the study (Figure 4).

### Quality of life

The OSA-18 instrument is a quality-of-life questionnaire focusing on pediatric sleep disordered breathing. It has been used as a screening tool for pediatric OSA (Franco et al., 2000). This questionnaire consists of 18 questions grouped into five subscales: sleep disturbance, physical symptoms, emotional distress, daytime function, and caregiver concerns. The 18 survey items are scored using a 7-point scale, where the parent/caregiver is asked to report how often during the previous 2–3 weeks their child has had specific symptoms using the following response scale: (1) none of the time, (2) hardly any of the time, (3) a little of the time, (4) some of the time, (5) a good bit of the time, (6) most of the time, and (7) all of the time. The total symptom score (TSS) may vary from 18–126 points. A TSS at or above 60 is considered abnormal and is associated with SDB. Scores of 60–80 suggest a moderate impact on the disease-specific quality of life and a score above 80 suggests a large impact (Franco et al., 2000).

OSA-18 questionnaire will be administered four times and parents/caregivers will rate the frequency of symptoms before and at the end of each treatment period (Figure 4).

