## Abstract

**Background:** Sleep-Disordered Breathing (SDB) varies from habitual snoring to partial or complete obstruction of the upper airway and can be found in up to 10% of children. SDB can significantly affect children's wellbeing, as it can cause growth disorders, educational and behavioral problems, and even life-threatening conditions, such as cardiorespiratory failure. Adenotonsillectomy represents the primary treatment for pediatric SDB where adeno-tonsillar hypertrophy is indicated. For those with craniofacial anomalies, or for whom adenotonsillectomy or other treatment modalities have failed, or surgery is contra-indicated, mandibular advancement splints (MAS) may represent a viable treatment option. Whilst the efficacy of these appliances has been consistently demonstrated in adults, there is little information about their effectiveness in children.

**Aims:** To determine the efficacy of mandibular advancement appliances for the management of SDB and related health problems in children.

**Methods/design:** The study will be designed as a single-blind crossover randomized controlled trial with administration of both an “Active MAS” (Twin-block) and a “Sham MAS.” Eligible participants will be children aged 8–12 years whose parents report they snore ≥3 nights per week. Sixteen children will enter the full study after confirming other inclusion criteria, particularly Skeletal class I or class II confirmed by lateral cephalometric radiograph. Each child will be randomly assigned to either a treatment sequence starting with the Active or the Sham MAS. Participants will wear the appliances for 3 weeks separated by a 2-week washout period. For each participant, home-based polysomnographic data will be collected four times; once before and once after each treatment period. The Apnea Hypopnea Index (AHI) will represent the main outcome variable. Secondary outcomes will include, snoring frequency, masseter muscle activity, sleep symptoms, quality of life, daytime sleepiness, children behavior, and nocturnal enuresis. In addition, blood samples will be collected to assess growth hormone changes.

**Trial registration:** This study was registered in the Australian New Zealand Clinical Trials Registry (ANZCTR): [ACTRN12614001013651].

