## Materials and methods

### Study design

This study will be carried out as a single-blind crossover randomized controlled trial. Each participant will wear two appliances consisting of an active MAS and non-active MAS (Sham MAS). Each appliance will be worn for a 3-week treatment period, which will be separated by a 2-week washout period. A similar study design and treatment time have been used in previous studies comparing the efficacy of MAS to nasal CPAP treatment in adults (Ferguson et al., 1996, 1997).

This study will be conducted in the Discipline of Orthodontics, School of Dentistry University of Otago, New Zealand. Ethical approval has been granted by the Human Ethics Committee at University of Otago [H14/054], and New Zealand Health Research South Ethics Committee- Southern District Health Board [01050]. The research has also been approved by Ngāi Tahu Research Consultation Committee (Research consultation with Māori).

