### Statistics

Data will be analyzed by SPSS (SPSS, IBM Corp. Version 22.0. Armonk, NY, USA) to perform descriptive statistics, and a mixed model analysis, and Bonferroni corrected *post-hoc* tests as appropriate. The significance level will be set at *P* = 0.05.

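### The OSA-18 recall of 2–3 weeks can outlast the 2-week washout, so the rating before period 2 can reach up to one week back into wear of the first appliance

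*Protocol article*

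**What the plan says.** The Quality of life section describes the OSA-18 as a parent-completed questionnaire in which the respondent is "asked to report how often during the previous 2–3 weeks their child has had specific symptoms". On timing it says: "OSA-18 questionnaire will be administered four times and parents/caregivers will rate the frequency of symptoms before and at the end of each treatment period". One of the four ratings therefore falls between the washout and the second treatment period.

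The Study design section fixes the durations: "Each appliance will be worn for a 3-week treatment period, which will be separated by a 2-week washout period". The Figure 4 legend repeats the washout length: "Treatment periods will be separated by a 2-week washout period".

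Quality of life is part of the second aim and appears in the Abstract's list: "Secondary outcomes will include, snoring frequency, masseter muscle activity, sleep symptoms, quality of life, daytime sleepiness, children behavior, and nocturnal enuresis". The Statistics section says that SPSS will be used "to perform descriptive statistics, and a mixed model analysis, and Bonferroni corrected" post-hoc tests. It does not say how the ratings taken before each period enter the model. Nothing in the article shortens the recall for the rating before period 2 or mentions that it may overlap the first treatment period.

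**The concern.** In a crossover, the rating before period 2 is meant to describe the child off treatment. A parent who looks back three weeks after a two-week washout also reports on the last week of the first appliance. The direction of this error depends on sequence, because the remembered week is active in one sequence and sham in the other. It is therefore systematic rather than random.

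Two uses of the rating are at stake. First, as a baseline for period 2, it would carry part of the first appliance's effect into the second appliance's change score. Second, it is the only OSA-18 evidence on whether quality of life returned to its starting level after washout. A remembered treatment week would look like an effect that had not worn off, and the two could not be separated afterwards.

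The recall window is fixed when the parent fills in the form. A later analysis plan can choose not to use the rating, but it cannot repair it. Because the wording gives a range, the amount of overlap may also differ between parents.

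**Working it through.** The article states no figure for this point, so there is none to reproduce. The check has four steps.

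**Inputs from the article**
- Recall R: 2 to 3 weeks (Quality of life).
- Washout W: 2 weeks (Study design; Figure 4 legend).
- Treatment period: 3 weeks per appliance (Study design).
- OSA-18 ratings: before and at the end of each period (Quality of life).

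**Assumptions**
- The rating before period 2 is made at the end of washout. Figure 4 itself is not available; an earlier rating would increase the overlap.
- The score is the equally weighted average over the recalled weeks.
- There is no true carry-over.
- The two sequences are balanced.

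**Step 1: overlap.** Overlap = max(0, R − W), and the contaminated fraction is f = overlap / R.

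| Recall R (weeks) | Overlap (weeks) | f |
|---|---|---|
| 2 | 0 | 0 |
| 2.5 | 0.5 | 0.5/2.5 = 0.20 |
| 3 | 1 | 1/3 = 0.33 |

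**Step 2: change-score contrast.** Set the untreated score to 0, and let tA and tS be the effects of the active and sham appliances (negative means improvement). The rating before period 1 is 0. The rating before period 2 is f·tA in the active-first sequence and f·tS in the sham-first sequence. Active change minus sham change is then:
- Active first: tA − (tS − f·tA) = (1 + f)·tA − tS
- Sham first: (tA − f·tS) − tS = tA − (1 + f)·tS
- Mean of the two: (1 + f/2)·(tA − tS)

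The multiplier 1 + f/2 is 1.00, 1.10 and 1.17 for R = 2, 2.5 and 3 weeks. The two sequences differ by f·(tA + tS), which would show as a spurious period effect. A period term does not remove the multiplier, because the period-adjusted estimate is this same mean over the sequences.

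**Step 3: illustrations with assumed effects, in OSA-18 points**

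| R (weeks) | tA, tS | True difference | Active first | Sham first | Mean |
|---|---|---|---|---|---|
| 2 | −10, 0 | −10 | −10.0 | −10.0 | −10.0 |
| 2.5 | −10, 0 | −10 | −12.0 | −10.0 | −11.0 |
| 3 | −10, 0 | −10 | −13.3 | −10.0 | −11.7 |
| 3 | −10, −3 | −7 | −10.3 | −6.0 | −8.2 |
| 3 | −5, −5 | 0 | −1.67 | +1.67 | 0 |

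The last row shows that equal effects shift the two sequences in opposite directions and leave the mean at 0.

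**Step 4: what is and is not touched**
- End-of-period scores: a recall of at most 3 weeks fits inside a 3-week treatment period, so the contrast is tA − tS in both sequences.
- Period-1 change: its baseline precedes any appliance, so there is no overlap.
- Washout check: the rating before period 2 minus the rating before period 1 is f·tA in the active-first sequence. With 3-week recall that is one third of the active effect (10/3 = 3.3 points of improvement when tA = −10), although nothing has carried over.

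**The case against.** The strongest objection is that the harm depends on an analysis the article does not specify. Rating before and after each period describes data collection. The Statistics section names a mixed model without committing to change scores or to the second baseline. How period baselines are used is properly left to an analysis plan that is not shown, and a comparison of end-of-period scores would be unaffected. This stands, so the inflation has to be stated as conditional. It does not cover the recall wording, which an analysis plan cannot change once parents have answered.

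A reader might infer that every change-from-baseline comparison is distorted, or that the overlap could by itself produce a positive result. The documents support neither. At 2-week recall there is no overlap, the period-1 change is clean, and under the averaging model a real difference is scaled up but none is created.

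The 17% is also the upper end under equal weighting. If parents give recent weeks more weight, it is smaller. If the second baseline is used as a covariate with a fixed slope b between 0 and 1, the same algebra gives 1 + b·f/2, again smaller.

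Finally, the consequence is limited. The Discussion already concedes subjective questionnaires and possibly limited power for secondary outcomes, and treats these mainly as descriptors for planning later studies. With 16 children and an assumed true effect of 0.5 SD of the paired difference, the standard error is 1/√16 = 0.25 SD and the largest bias is 0.5/6 = 0.08 SD, about one third of a standard error. At an assumed effect of 1.0 SD the bias is 1/6 = 0.17 SD, about two thirds of a standard error. This also stands and keeps the severity low. However, because the article wants these results to inform later research, an exaggerated effect size would still be unhelpful.

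**Conclusion.** The mismatch is real but minor. The stated recall range can exceed the stated washout, so the OSA-18 rating before period 2 can include from zero up to one week on the first appliance. If that rating is used as a change-score baseline, the active-minus-sham estimate is inflated by 0% to 17% (10% at 2.5 weeks). This rests on equal weighting of the recalled weeks, no true carry-over, balanced sequences and a rating made at the end of washout. The rating is also an unreliable check on whether washout was complete.

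It would be wrong to read this as a flaw in the crossover as a whole. The primary outcome, AHI, comes from overnight recording and has no recall window. The OSA-18 is the only questionnaire for which the article states one. Low severity, confined to one secondary outcome.

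**What to change.** Set the OSA-18 recall at the previous 2 weeks for all four ratings. This is the lower end of the range already stated, and it lies within each treatment period. It matches the washout exactly, with no margin, so the rating before period 2 should be completed at the end of washout. The overlap is then 0 and the multiplier is 1.00.

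If the present wording is kept, or forms have already been completed with it, base the OSA-18 treatment effect on end-of-period scores, active against sham, with period in the model. Do not use the rating before period 2 as a baseline, and do not read it as evidence on washout.

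The cost is one line on the form or one sentence in the analysis section. No visit, appliance or treatment schedule changes. The downsides are a slightly shorter recall than the upper end of the present range, and a single fixed window in place of the range given for a cited questionnaire, which should be noted when the results are reported.
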